**Fig. 2 Fig2:**
[figure not shown]
Schedule of enrollment, interventions, and assessments. Completed SPIRIT 2013 figure of recommended content for the schedule of enrolment, interventions, and assessments

#### Secondary outcomes

Secondary outcome measures are Spence Children’s Anxiety Scale (SCAS) [45] and Children’s Anxiety Life Inference Scale (CALIS) [46].

SCAS [45] is a questionnaire for children and parents assessing the severity of anxiety symptoms broadly in line with the dimensions of anxiety disorders proposed by the DSM-IV. It consists of 44 items for the children and 39 for the parents rated on a Likert scale ranging from 0 (never) to 3 (always). The scale assesses six domains of anxiety disorders, including generalized anxiety, panic/agoraphobia, social phobia, separation anxiety, OCD, and physical injury fears (specific phobia). These scales can be scored separately or added together for an overall anxiety disorder score. The Danish version of SCAS has shown excellent internal consistency for the total scale (α = 0.89) in a sample of youths with anxiety disorders and good test–retest reliability after 2 weeks (*r* = 0.84) and 3 months (*r* = 0.83) [47].

CALIS [46] is designed to assess life interference attributed to fears and worries from the child and parent perspectives. The measure targets interference in the child’s life (e.g., school, leisure time, and friendships) rated on nine items and in the parent’s/family’s life (e.g., relationships with friends and family, career, and level of stress) rated on 16 items. The items are rated on a Likert scale with the interference rated from 0 (not at all) to 4 (a great deal) and the scale has demonstrated satisfactory internal consistency on subscales for both youth (α range = 0.70–0.84) and parent ratings (α range = 0.75–0.90) and moderate stability for a 2-month retest period (*r* range = 0.62–0.91) [46].

#### Other outcomes

ADHD will be assessed using the Attention Deficit/Hyperactive Disorder-Rating Scale (ADHD-RS) [48], and depression and OCD with the parts of the ADIS that address these disorders [35].

Further, social and communicative skills will be assessed using parent and teacher rating scales from the Social Responsiveness Scale (SRS) [49], behavioral and emotional problems will be assessed with the Strengths and Difficulties Questionnaire (SDQ) [50] using both parent and teacher ratings. A developmentally sensitive, general measure of negative self-statements across both internalizing and externalizing problems will be obtained by the use of Children’s Automatic Thoughts Scale (CATS) [51]. In addition, children’s adaptive skills will be assessed with the Adaptive Behavior Assessment System, Second Edition (ABAS-II) [52]. Baseline characteristics regarding socioeconomic status and parenthood will be obtained by questions concerning level of education, employment, household income, etc. In addition, parent’s quality of life will be examined with the WHO-five Well-being Index [53]. Finally, the Experience of Service Questionnaire will assess the children’s and parents’ satisfaction with the treatment [54].

### Sample size

Previous studies have shown that 71.4% of CBT-treated children with ASD and anxiety disorders no longer fulfilled the diagnostic criteria for their primary anxiety disorder (i.e., most severe anxiety disorder based on parents response to ADIS) following treatment, which is markedly greater than for the WL control group, in which none had recovered [25]. Below, we will make the conservative assumption that, at T2, 60% of the CBT participants and 10% of the WL group will no longer fulfil the primary anxiety disorder diagnosis identified at T1 (Fig. 1). Applying a significance level of 5%, it is then estimated that 34 participants (17 in each group) will be needed to obtain a statistical power of 80% to reject the null hypothesis of no difference between these proportions. This calculation is based on a simple two-sided comparison of proportions by Fisher’s exact test without adjustment for blocking, sex, or co-morbidity of disorders other than anxiety disorders. We do not expect the inclusion of these factors to affect the power substantially. Thus, under these assumptions, 50 participants will be enrolled.

### Analysis

The primary outcome will be measured as a dichotomous variable, as one (1) if the primary anxiety disorder identified before treatment (at time point T1) persists post treatment (T2) and as zero (0) if the child no longer fulfils diagnostic criteria for the primary anxiety disorder at T2.

The overall percentage of children free of primary anxiety disorder will be calculated and the effect of the intervention will be measured in terms of odds ratio, comparing odds for recovery in the treatment condition with the corresponding odds in the control condition. This will be calculated by conditional logistic regression and with adjustment for sex and co-morbidity (yes/no) by diagnoses other than anxiety disorders and ASD.

A mixed between–within analysis of variance (ANOVA) design will be used for all continuous outcomes to further evaluate the effect of the CBT intervention. Possible reduction in scale scores on CSR, SCAS, CALIS, ADHD-RS, SDQ, SRS, CATS, and ABAS-II, together with measures of parent’s quality of life, will be investigated to test for differences between CBT and WL groups while comparing pre and post measures within the two groups.

Analysis of the treatment effect such as direct comparison between T1/T1’ and T3/T3’ or changes over time (from T1/T1’ via T2/T2’ to T3/T3’) in the different scale scores may also be considered regarding further elucidation of CBT efficacy.

In order to enhance the strength of the analysis regarding continuation at follow-up (T3 and T3’) of the treatment effect seen at T2 and T2’, the possibility of combining CBT and WL groups will be investigated. However, we are aware that baseline levels at T1’ can be different from T1 due to natural fluctuation, which means that the two samples may not compare well. Thus, combining the samples will only be done after investigating such possible differences at baseline levels.

Repeated measures (longitudinal) analyses will be used when relevant. It is unlikely that the same probability distribution can be used for all secondary outcomes and statistical inference will determine which to apply. For some measures, a normal distribution may be applied, whereas other measures are nominal or at best ordinal.

Though measures will be taken to avoid this, it is expected that a few children in both the CBT group and among the WL will drop-out during the study. The impact of this will be investigated and, if possible, handled by, for example, multiple imputation. Unless participants withdraw the consent to participate, all available data will be used for the analyses in an intention-to-treat analysis under the assumption that data are missing at random. Statistical analyses will be conducted by the use of STATA (StataCorp, College Station, Texas, USA) and the significance level will be set at a *P* value of less than 0.05.

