After being referred to assessment for the study and before randomization, possible anxiety disorders are assessed by using the structured interview Anxiety Disorders Interview Schedule for DSM-IV: Parent & Child interview schedule (ADIS-IV-C/P) [35], which will be described in detail in the outcome section below. The ADIS-IV-C/P and questionnaires regarding secondary and other outcomes are distributed approximately 2–3 weeks before commencement of either CBT treatment or the WL period.

Treatment then runs for 10 sessions over a 13-week period. At the end of treatment, for ethical purposes, the WL control group will be offered the same CBT program as the trial group. This will be carried out in groups with fewer than five children if some of the WL children decide not to accept this offer.

Following treatment or WL period, and again at a 3 month follow-up (after treatment), the families will be interviewed with the ADIS-IV-C/P and asked to answer the questionnaires again.

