### Randomization

To control for the potential experience of therapists and to limit time between assessment and treatment, allocation to CBT treatment or WL control group will be performed using blocked randomization. Each block will comprise 10 participants and, within each block, allocation to either the WL control group or the treatment group will in a 1:1 allocation ratio. For each child, at least one of their parents participates and the total number of persons in each group may therefore vary.

In practice, randomization will be performed as follows:

From the total pool of 252 possible different sequences of five CBT and five WL allocations (e.g. {WL, WL, WL, CBT, CBT, WL, CBT, CBT, WL, CBT}), one is picked at random for each of five blocks and the allocations are written on a text file together with a unique five-digit subject identification number. These block-specific files are being generated by a statistical consultant (blind for the therapists and the project manager) and each file will not be opened before the next (the first) 10 children are ready for randomization. The children are numbered 1 to 10 before opening the file and child 1 will then be allocated to the condition noted for subject 1 in the file, child 2 to the condition noted for subject 2, etc.

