The disorders are rated with a clinical severity rating (CSR) from 0 (no interference) to 8 (extreme interference) with severity ratings of 4 or above signifying the presence of a clinical disorder. The assessor’s CSR score, which is based on a combination of the parent and child’s CSR score plus a clinical evaluation of the extent of severity, will be used in assessing the disorder with the most impairing diagnosis considered the primary diagnosis.

The ADIS-IV-C/P has previously demonstrated good-to-excellent 7–14 days test–retest reliability for the presence of specific diagnoses (Cohen’s Kappa [κ] range for different diagnoses = 0.71–0.84 for children interviews and 0.73–0.92 for parent interviews) [42]. High concurrent validity against the Multidimensional Anxiety Scale for Children [43] has also been demonstrated [44].

The ADIS-IV-C/P assessment will be performed by a group of trained psychiatrists, psychologists or psychology students blinded to treatment conditions under supervision of a senior assessor at the Anxiety Disorder Clinic for Children and Adolescents, Department of Psychology and Behavioural Science, Aarhus University.

Inter-rater reliability will be conducted by two trained assessors based on 10% of the video recorded interviews selected randomly.

For the CBT group, the ADIS-IV-C/P interview will be completed at pre, post, and follow-up 3 months after the last session (T1, T2, and T3) and pre and post for the WL group (T1 and T2). A similar set of measures at the post and 3-month follow-ups will be obtained from the WL group after their receipt of the CBT treatment following the WL period (T1’ = T2, T2’, and T3’). For an overview of the schedule of enrolment, interventions, and assessments please see Fig. 2 for the completed SPIRIT Figure.

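### The primary logistic model leaves out baseline CSR, a value already collected that sets how far each child must improve to count as recovered; the cost is some precision, not validity

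*Protocol article*

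**What the plan says.** The Analysis section defines the primary outcome as binary: one if the primary anxiety disorder found at T1 is still present at T2, and "as zero (0) if the child no longer fulfils diagnostic criteria for the primary anxiety disorder at T2". For the treatment odds ratio it specifies conditional logistic regression, "with adjustment for sex and co-morbidity (yes/no) by diagnoses other than anxiety disorders and ASD". No other covariate is named, and no reason is given for leaving severity out.

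The Primary outcome section rates each disorder with a CSR from 0 to 8, "severity ratings of 4 or above signifying the presence of a clinical disorder". The assessor's CSR "will be used in assessing the disorder with the most impairing diagnosis considered the primary diagnosis".

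That rating exists for every child at baseline. The Study procedure section says: "After being referred to assessment for the study and before randomization, possible anxiety disorders are assessed by using the structured interview"; Table 2 schedules the interview at T1 in both arms. The Randomization section does not stratify on severity; it states only blocking: "Each block will comprise 10 participants", allocated 1:1.

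CSR otherwise enters the analysis as an outcome in its own right: "A mixed between–within analysis of variance (ANOVA) design will be used for all continuous outcomes", and CSR heads the list of scales.

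**The concern.** The endpoint is a threshold on the scale that is also measured at baseline. Two children who improve by the same amount can be classified differently only because they started at different points. Sex and co-morbidity have no such built-in link to the outcome.

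Leaving out a prognostic baseline value has two consequences in a trial of 50. A chance difference in starting severity between the arms feeds into the estimated odds ratio with no correction. Power is also lower than it could be if the true effect is smaller than planned, and the Discussion section itself says the trial is underpowered in that case.

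The covariate list is written into the article, so this is a choice the document makes, not a detail deferred to an analysis plan.

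**Working it through.** **1. The plan's own figure.** Inputs from the Sample size section: 60% versus 10% recovery, two-sided 5%, Fisher's exact test, 80% power. Exact enumeration gives power of 78.6% at 16 per group and 82.7% at 17. The stated 17 per group (34 in all) reproduces; 50 are to be enrolled.

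**2. Dependence of the endpoint on T1 CSR.** A diagnosis needs CSR of at least 4, so recovery means CSR of 3 or less. Required fall = T1 CSR − 3: one point from 4, five points from 8. A child with a primary disorder at T1 has a CSR between 4 and 8.

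**3. Chance imbalance, 25 per arm.** In SD units the standard error of the difference in means is √(2/25) = 0.283. For a difference above 0.4 SD, z = 0.4/0.283 = 1.41 and the two-sided probability is about 16%. With an assumed SD of 1.04 CSR points, the standard error is 1.04 × 0.283 = 0.30 points, and a difference of 0.5 points or more occurs in about 9% of trials.

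**4. Power with and without T1 CSR.** The documents give neither the CSR distribution nor its association with recovery. Assumed: CSR 4 to 8, mean 5.9, SD 1.04; odds ratio for recovery per CSR point 1.00 (not prognostic), 0.62, 0.38 or 0.24. For each cell, 6,000 trials of 25 per arm were simulated and analysed with ordinary logistic likelihood-ratio tests at 5%, with sex and co-morbidity in both models and no block term. Entries are power (%) without → with CSR.

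| Recovery | OR 1.00 | OR 0.62 | OR 0.38 | OR 0.24 |
|---|---|---|---|---|
| 60% vs 10% | 97.9 → 97.8 | 98.2 → 98.5 | 98.1 → 99.3 | 98.0 → 99.6 |
| 45% vs 10% | 83.0 → 82.5 | 84.1 → 84.9 | 82.5 → 87.8 | 84.1 → 92.0 |
| 40% vs 10% | 73.4 → 73.4 | 73.6 → 75.2 | 72.9 → 79.4 | 74.1 → 84.3 |

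Changes, left to right: −0.1, 0.3, 1.2 and 1.6 points at 60% vs 10%; −0.5, 0.8, 5.3 and 7.9 at 45%; 0.0, 1.6, 6.5 and 10.2 at 40%.

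A smaller simulation used another assumption (T1–T2 severity correlations of 0.3, 0.5 and 0.7) and Firth logistic regression without a block term, 700 trials per cell. At 40% vs 10% it gave 71.6 → 72.9, 70.3 → 77.9 and 71.0 → 84.3. The Monte Carlo standard error of each figure is about √(0.71 × 0.29/700) = 1.7 points, so the first gain is not distinguishable from noise. The other two show the same pattern; the last, 13.3 points, shows that the upper end depends on the strength assumed.

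**5. Sparse data.** Expected wait-list recoveries: 10% × 25 = 2.5. Expected total at the planned rates: 0.60 × 25 + 2.5 = 17.5. With treatment, sex and co-morbidity that is 17.5/3 = 5.8 recoveries per coefficient; with CSR, 17.5/4 = 4.4. With no true effect (10% in both arms), the unpenalised test rejected in 7.5–8.8% of trials without CSR and 9.4–10.4% with it. In a small conditional-logistic run on blocks of 10 (200 trials per scenario), about 8–11% of fits with CSR showed near-separation. Firth fits with CSR, without a block term, rejected in 2–4%.

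**6. Change of estimand.** At 60% vs 10% the marginal log odds ratio is ln[(0.6/0.4)/(0.1/0.9)] = ln 13.5 = 2.60. Conditional on CSR, with an odds ratio of 0.38 per point, the same recovery rates correspond to 3.07.

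**The case against.** The strongest reply is that nothing here is misstated. The covariates are named in advance, the Sample size section refers to the same two, and randomisation makes the comparison valid without CSR. The error rate of a valid test already allows for chance imbalance, and the 16% figure would apply to any baseline variable in a trial of this size. All of that stands. A reader might infer from the omission that the treatment estimate is biased or that 50 children are too few. The documents support neither: no bias over repeated trials follows, and the sample size reproduces.

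A reader might also infer that T1 CSR must be the strongest predictor of recovery. The threshold arithmetic makes prognostic value plausible, but the documents do not measure it or rank it against co-morbidity. At the trial's own design effect the gain is negligible whatever strength is assumed.

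It is also fair that adding CSR to an unpenalised fit could do harm, given the null rejection rates above. That is a reason to couple the covariate with penalisation, not a reason to omit it.

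Finally, CSR is analysed pre to post in the mixed ANOVA, and the Abstract names severity beside diagnostic status as a primary outcome. That uses the starting level for the severity result, but does nothing for the binary result on which the trial is sized.

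**Conclusion.** The point holds as one of efficiency. The primary model omits a baseline value that is collected on every child before randomisation and fixes the distance to the endpoint. The consequence is lost precision and no correction for chance imbalance in severity. It is neither a bias nor a sample-size error.

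Size: about 0 to 2 points of power at 60% vs 10%, and 0 to about 10 points at 40% vs 10%. Both ranges rest on an assumed CSR distribution and assumed prognostic strength. They come from unpenalised fits without blocks whose null rejection exceeds 5%, so the comparison within each cell matters more than the absolute level. If CSR is not prognostic there is no gain, and in these runs the loss was at most half a point.

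The stronger conclusion that sex and co-morbidity should give way to CSR is not supported. Dropping them would ease the sparse-data problem, but the documents offer no evidence that they are the weaker covariates. That is an optional trade-off.

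**What to change.** In the Analysis section, before outcome data are examined:

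- Add T1 CSR of the primary disorder, as a linear term, to sex and co-morbidity in the primary model.
- Fit that model with Firth penalisation and test treatment by the penalised likelihood-ratio test.
- State how the randomisation blocks are handled. The present wording implies conditioning, presumably on blocks; a Firth fit must say whether blocks enter as indicator terms, are conditioned on, or are left out. The Firth results above had no block term, so the chosen form should be checked by simulation for null rejection and separation.
- Report the risk difference beside the odds ratio.
- Keep the model without CSR as a sensitivity analysis. Moving sex and co-morbidity to a sensitivity model is optional.

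The cost is analysis wording plus that simulation check; no new data are needed. The odds ratio becomes conditional on severity and will not be directly comparable with an odds ratio that is not, which is why the risk difference should accompany it. There is little or no return if CSR proves not to be prognostic.

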**Methods:**

This study is a randomized controlled trial (RCT). Fifty children with ASD and anxiety, aged 7 to 13 years, will be randomly assigned to group CBT or a wait-list control (WL) condition. The design will follow a two (CBT and WL) by two (pre–post assessment) mixed between–within design. The control group will receive intervention after the waitlist period of 13 weeks. Primary outcomes are diagnostic status and severity of the anxiety disorders, measured with The Anxiety Disorder Interview Schedule for DSM-IV, Parent and Child Versions. Secondary outcomes are parent and child ratings on questionnaires on the child’s level of anxiety and impact on everyday life. Additional outcomes entail information gathered from parents, child and teachers on the child’s behavior and negative self-statements, together with social and adaptive skills. Follow-up data will be collected 3 months after intervention.

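### Continuous outcomes are to be tested by a 2×2 mixed ANOVA, which is the change-score test; comparing T2 adjusted for T1 and randomisation block is more precise at negligible cost

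*Protocol article*

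**What the plan says.** The Analysis section of the protocol article fixes the method: "A mixed between–within analysis of variance (ANOVA) design will be used for all continuous outcomes". It lists CSR, SCAS, CALIS, ADHD-RS, SDQ, SRS, CATS, ABAS-II and parent quality of life, and gives the aim as to "test for differences between CBT and WL groups while comparing pre and post measures within the two groups". The abstract fixes the layout: "The design will follow a two (CBT and WL) by two (pre–post assessment) mixed between–within design".

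For these outcomes neither the T1 score nor the block is named as a covariate. The Randomization section does allocate in blocks: "Each block will comprise 10 participants", with five blocks and equal allocation within each.

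On missing data the Analysis section says that "all available data will be used for the analyses in an intention-to-treat analysis under the assumption that data are missing at random". It also foresees multiple imputation where possible and repeated-measures analyses where relevant, without tying either to a particular outcome.

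CSR is not a minor outcome here. The abstract counts severity of the anxiety disorders among the primary outcomes, although the Primary outcome section names diagnostic status only.

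**The concern.** A 2×2 mixed ANOVA uses the baseline by subtracting it, which fixes its coefficient at 1. The most precise coefficient is the regression slope of T2 on T1, which is below 1 whenever r is below 1 and the two SDs are equal. Subtracting the whole baseline therefore adds noise that randomisation makes unnecessary. The Discussion concedes that 50 children can show only a relatively large effect, so precision that can be had without recruiting anyone is worth taking.

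Two further points follow. Block structured the allocation but has no named place in this model. And the arm-by-time contrast draws only on children who have both T1 and T2, although the article expects some dropout in both arms.

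**Working it through.** **The plan's own figure.** The only sample-size figure is for diagnostic status: 17 per group for 80% power at 60% versus 10%. Exact enumeration of two-sided Fisher power gives 78.6% at 16 per group and 82.7% at 17, so the figure reproduces. Nothing below affects it. No SD, effect size or power is stated for any continuous outcome.

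**Inputs.**
- N = 50 (Sample size: "Thus, under these assumptions, 50 participants will be enrolled"), equal allocation, hence 25 per arm; five blocks of 10 (Randomization); 5% significance level.
- Retest correlations from the Secondary outcomes section: SCAS 0.83 at 3 months (reported there as "good test–retest reliability after 2 weeks" and at 3 months); CALIS 0.62 to 0.91 at 2 months. These stand in for r. Variable response to treatment would probably lower r, so they are more likely too high than too low.
- Assumed, not in the article: r = 0.5 as a lower case, a true effect of 0.5 SD, and equal T1 and T2 SDs.

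**Step 1: identity.** In a simulated data set of 50 children, the arm-by-time F was 5.994 on 48 df and the squared t from the change-score test was 5.994.

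**Step 2: variances.** With T1 and T2 SDs s1 and s2:
- change score: s1² + s2² − 2·r·s1·s2
- ANCOVA: s2²(1 − r²)
- difference: (s1 − r·s2)², which is never negative.

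With equal SDs the ratio of ANCOVA to change-score variance is (1 − r²)/[2(1 − r)] = (1 + r)/2.

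**Step 3: small-sample cost.** Estimating the slope multiplies the ANCOVA variance by about 1 + 1/(N − 4) = 47/46. The gain vanishes when (1 + r)/2 × 47/46 = 1, that is at r = 2 × 46/47 − 1 = 0.957, about 0.96.

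**Step 4: size at N = 50.** For example, at r = 0.62: 0.81 × 47/46 = 0.828; √0.828 = 0.910, so the SE falls by 9.0%; 50/0.828 = 60.4 children. Power is from the noncentral t with 48 df (change score) and 43 df (ANCOVA plus four block terms), for a true effect of 0.5 SD.

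| r | variance ratio | SE reduction | equivalent N | power, change score | power, ANCOVA + block |
|---|---|---|---|---|---|
| 0.50 (assumed) | 0.766 | 12.5% | 65 | 41% | 51% |
| 0.62 | 0.828 | 9.0% | 60 | 51% | 59% |
| 0.83 | 0.935 | 3.3% | 53 | 84% | 87% |
| 0.91 | 0.976 | 1.2% | 51 | 98.3% | 98.5% |

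The smallest difference detectable with 80% power moves from 0.71 to 0.64 SD at r = 0.62, and from 0.47 to 0.46 SD at r = 0.83.

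**Step 5: block.** If block has no effect, its four df cost at most about 0.2 points of power. If block explains 5% of T2 variance (assumed), simulated ANCOVA power at r = 0.62 rises from 58.5% to 61.0%.

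**Step 6: missing T2.** Under no treatment effect and unit SDs, the expected change given T1 is −(1 − r)·T1. If the retained children's mean T1 differs between arms by Δ, the complete-case change score is biased by (1 − r)·Δ in size. In simulations where T2 missingness depended on T1 differently by arm, the bias was 0.126 SD at r = 0.62 and 0.056 SD at r = 0.83. Both correspond to Δ of about 0.33 SD (0.126/0.38 and 0.056/0.17). Rejection under the null was 7.7% and 5.6%. ANCOVA on the same children had a bias of −0.001 SD and rejected about 5%. With complete data both methods rejected about 5% (checked at r = 0.62).

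**The case against.** The strongest reply has four parts.

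**The gain may be small.** At the only 3-month SCAS correlation cited, 0.83, the SE falls by 3% and power at 0.5 SD rises by about 2 points. The Background cites effects near 1.2 SD for clinician- and parent-rated anxiety. At 1.2 SD the change-score test already has 98.6% power at r = 0.5. This stands: the gain in power matters only if the effect is well below the cited one and r is moderate. A narrower confidence interval is still useful at any effect size.

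**Missing data are already covered.** A reader might infer that the ANOVA contradicts the intention-to-treat and missing-at-random statement. The article does not support that. It nowhere specifies a complete-case analysis, and it names multiple imputation and longitudinal models as options. What remains is that the ANOVA alone does not deliver the use of all available data, and neither option is attached to these outcomes. Plain ANCOVA shares the limitation, since it also drops children without T2.

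**Adjustment is not free, nor better in every sample.** It costs 1 df for T1 and 4 for block, and above r of about 0.96 the change score is no worse. This stands, but no cited correlation is that high.

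**It is only a choice between valid methods, and covariates may be left to the full plan.** With complete data the planned test is unbiased, and the powered analysis is the binary one. But the article does not leave the method open: it prescribes the mixed ANOVA for every continuous outcome. It also reserves other distributions for measures that turn out nominal or ordinal, so the point applies only to outcomes analysed as continuous.

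**Conclusion.** The point holds as a loss of efficiency, not as an error. The arm-by-time test is the change-score test, and adjusting T2 for T1 is at least as precise for any r up to about 0.96 at this sample size. The saving in standard error runs from about 12.5% (r = 0.5, assumed) through 9% (r = 0.62) to 3% (r = 0.83) and 1% (r = 0.91). These figures assume equal SDs at T1 and T2, and the r that will apply under treatment is unknown. The power figures also assume a true effect of 0.5 SD.

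The bias in Step 6 is conditional. It arises only if the ANOVA is run on complete cases and T2 missingness depends on T1 differently by arm.

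A reader might also infer that the trial is undersized or its main test compromised. Neither follows: the diagnostic-status analysis and its sample size are untouched. The outcomes affected are SCAS, CALIS, the other continuous scales, and CSR severity, which the abstract counts as primary. The change is worth making.

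**What to change.** For each outcome treated as continuous and measured at T1 and T2 (T1' in the WL arm), replace the mixed ANOVA with one of two models. The outcomes are CSR, SCAS, CALIS, ADHD-RS, SDQ, SRS, CATS and parent quality of life.

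1. A likelihood-based longitudinal model of T1 and T2 with a common baseline mean across arms, plus block. This keeps children who lack one of the two scores.
2. ANCOVA of T2 on arm, T1 and block, combined with the multiple imputation the article already foresees.

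Name one of them in advance, and report the adjusted T2 difference with its 95% CI.

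Treat ABAS-II separately. Table 2 shows it at T1 and T3 in the CBT arm and at T1' and T3' in the WL arm. The CBT arm therefore has no T2 and the WL arm no T1, and neither the planned ANOVA nor the models above can be run. Either the schedule or the list of outcomes analysed this way has to be reconciled.

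The cost is a change of analysis wording, 1 df for T1 and 4 for block. No new data, visits or participants are needed.
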